#### Postoperative course

Need of the post-operative intensive care unit (ICU), length of ICU stay, postoperative LOS, and discharge settings are all registered. Thirty-day postoperative morbidity is collected and classified according to Clavien–Dindo classification [25, 26]. Cumulative burden of postoperative complications is calculated for each patient according to the comprehensive complication index [27]. If re-intervention is needed, the reason for reintervention, operative procedure, approach, and need for postoperative ICU stay are all collected (Table 6).

**Table 6 Tab6:** Postoperative course

POSTOPERATIVE COURSE	POSSIBLE ANSWERS
ICU stay	yes/no
Length of ICU stay	value [days]
Postoperative length of stay	value [days]
Discharge/transfer setting	Other ward Rehabilitation Home Nursing home
Complications according to Clavien–Dindo	yes/no (if yes user should report type of complication and grade)
Anastomotic leak?	yes/no
Bleeding requiring transfusion?	yes/no
ICU transfer because of postoperative complications?	yes/no
Re-intervention within 30 days?	yes/no
Re-intervention reason	[specify]
Re-intervention: procedure	[specify]
Pre-reintervention setting	Surgical ward Other ward ICU Home
Post-reintervention ICU stay	yes/no

#### Pathology

The pathology report includes cancer type and grade of differentiation according to the WHO classification [28], the number of retrieved and positive lymph-nodes, and lympho-vascular and perineural invasion. For patients with rectal cancer, additional information includes extra mural vascular invasion (EMVI), evaluation of distal and circumferential margins, TME quality according to the Quirke classification [29, 30], and grade of regression following neoadjuvant treatment according to Ryan/CAP [31]. Final tumor stage is reported according to the 7th edition of the TNM cancer staging system [32] (Table 7).

**Table 7 Tab7:** Pathology and postoperative oncological treatment

PATHOLOGY	POSSIBLE ANSWERS
Histological type	[User should report histologic type of tumour]
Number of lymph-nodes retrieved	value
Number of metastatic lymph-nodes	value
Grade of differentiation	Low/high
Lymphatic invasion	yes/no
Vascular invasion	yes/no
Perineural invasion	yes/no
pTNM	[User should report pathologic tumour-node-metastasis staging]
Pathology — rectal cancer	
EMVI	
Free distal margin	yes/no
Free radial margin	yes/no
TME quality according to Quirke	Grade 1 Grade 2 Grade 1 Not assessed
Grade of regression after neoadjuvant therapy	Grade 0 Grade 1 Grade 2 Grade 3 Not assessed
pTNM	[User should report pathologic tumour-node-metastasis staging]
Postoperative chemotherapy	yes/no
Postoperative radiotherapy	yes/no

#### Follow-up

After hospital discharge, any postoperative oncological treatment will be reported (adjuvant chemotherapy and/or radiation therapy). Possible changes in living conditions, considered as a proxy for functional recovery, will be reported. Any emergency department access until postoperative day 30 and the reason for it will be collected as well as the need for re-hospitalization. Mortality at 30, 90, and 180 days postoperatively will be collected, together with the cause of death (Table 8).

**Table 8 Tab8:** Follow up

30 DAYS - FOLLOW UP	POSSIBLE ANSWERS
Emergency room access because of surgical complications	yes/no
Re-admission from first surgery	yes/no
Reason for readmission	surgical complication complication not related to surgery other
In-hospital death	yes/no
Cause of death	Disease progression Complications other medical issues unknown
Patient status at 30 days	alive/death

90 DAYS – FOLLOW UP	
Patient status at 30 days	alive/death

180 DAYS – FOLLOW UP	
Patient status at 30 days	alive/death

## Statistical considerations

All the analyses will be performed considering tumor location (colon or rectum) as a stratification factor. For continuous variables, the arithmetic mean and standard deviation (SD), as well as the median value and minimum–maximum, will be presented. Absolute frequencies together with the percentage relative frequencies will be reported while summarizing qualitative variables.

To evaluate the performance of surgical activity, absolute numbers and relative percentages of each performance indicator reported will be calculated. The mortality rate will be defined as the number of patients who died within 30, 90, and 180 days after surgery. Graphical representation will also be used: funnel plots will be displayed for each KPI, both in unadjusted and adjusted versions.

Appropriate statistical models (i.e., mixed models, logistical regression, multilevel models) will be developed to evaluate the relationship among analyzed indicators and potential explanatory factors as well as for standardization/adjustment purposes. Main covariates will include age, gender, ASA score, CCI, surgery setting (urgent vs. elective), and ECOG.

Hospitals will be used as random effects to account for the presence of possible variability among hospitals. Other exploratory subgroup analyses will be performed.

Furthermore, to assess the effects of continuous monitoring and benchmarking on clinical outcomes, a before-and-after approach will be used. Specifically, assuming the time from the first subject surgery until the release of the first benchmarking report as the reference period (baseline, i.e., “before” period), the analysis will evaluate any significant changes occurred afterwards. Any changes on the outcomes will be, therefore, attributed to the benchmarking effect.

Missing values will be replaced and estimated using multiple imputations. A two-sided 95% confidence interval (95% CI) will be reported as appropriate.

Statistical analysis will be performed using R statistical software (v. 4.0.6) — www.r-project.org.

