### Key performance indicators, case-mix, benchmarking, and feed-back activity

A core set of key performance indicators (KPIs) will be assessed to measure performance and evaluate the quality of colorectal cancer surgery across the participating centers (Table 2). Each KPI will be estimated both as unadjusted and risk adjusted for differences in patients’ characteristics for a fair comparison among the participating hospitals.

**Table 2 Tab2:** Overview of the selected key performance indicators

**ID**	**Indicator title**	**Indicator description**	**Indicator type**
1	Multidisciplinary discussion	Rate of patients discussed at a multidisciplinary meeting (MDM) before surgery	Colon and rectal cancer
2	Neoadjuvant treatment	Rate of patients receiving neoadjuvant treatment (radiation therapy, chemo-radiation, chemotherapy, total neoadjuvant treatment)	Rectal cancer
3	Minimally invasive resections	Rate of patients undergoing minimally invasive resection	Colon and rectal cancer
4	Conversion	Conversion rate from minimally invasive to open surgery at any time during the procedure	Colon and rectal cancer
5	Anastomotic leak	Rate of anastomotic leakage	Colon and rectal cancer
6	Anastomosis	Rate of patients undergoing anastomosis after low anterior resection	Rectal cancer
7	Loop ileostomy	Rate of loop ileostomy creation after low anterior resection	Rectal cancer
8	Length of stay (LOS)	Rate of patients discharged within postoperative days 3 and 5	Colon and rectal cancer
9	Postoperative complications	Rate of patients with severe postoperative complications (grade ≥ 3 according to Clavien–Dindo classification)	Colon and rectal cancer
10	Quality of total mesorectal excision (TME)	Rate of patients with TME grade 1 or 2	Rectal cancer
11	Positive circumferential resection margins (CRM)	Rate of reported positive CRMs (less than or equal to 1 mm)	Rectal cancer
12	Lymph-nodes yield	Rate of patients for who received adequate lymphadenectomy (≥ 12 lymph-nodes)	Colon and rectal cancer
13	Unplanned reintervention	Rate of patients with an unplanned return to theatre within 30 days after index surgery	Colon and rectal cancer
14	Unplanned readmission	Rate of patients with unplanned readmission within 30 days after discharge/transfer from surgical unit	Colon and rectal cancer
15	Postoperative mortality	Rate of patients who died 30,90, or 180 days after surgery	Colon and rectal cancer

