Every 12 months, an anonymized report on volume and KPIs will be delivered to each hospital comparing data of all the participating centers. A set of relevant case-mix variables (patients’ frailty, tumor burden, type of surgery) will be also identified in order to produce a reliable comparison of outcomes between hospitals and give each center case-mix adjusted outcomes.

Data collected during the first 18 months (from April 2019 to October 2020) will be analyzed in order to evaluate preliminary results on primary and secondary outcomes. The first preliminary analysis will be used as benchmark to further implement the auditing activity.

Case-mix adjusted data will be presented using funnel plots with a 95% confidence interval (Fig. 2).

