### Data collection and quality control

The data collection and management for this paper are performed using the OpenClinica open-source software for Electronic Data Capture (EDC), version 3.1 (Copyright OpenClinica LLC and collaborators, Waltham, MA, USA, www.OpenClinica.com). Case report forms are filled in for each patient by trained healthcare providers (attendings, residents) or properly trained data managers. Operative and postoperative data are retrieved both from electronic medical charts and administrative databases. Surgical data analysis, including detection of postoperative complications, will be done under the supervision of a staff surgeon.

Quality control and data authenticity will be performed by data managers and clinical research coordinators. Clinical data will be compared to routinely collect administrative information retrieved from regional registries to ensure reliability and completeness and to avoid selection bias. Registration of each patient is automatically linked to the regional administration database, which by law receives notification on all patients deceased in Emilia-Romagna.

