With the paramount of a concrete enhancement of postoperative outcomes and a reduction of costs, ESCA aims to investigate, for the first time in Italy, the impact of systematic clinical auditing and feedback in the field of colorectal cancer surgery among a large population representative of a real-world population. Key performance indicators based on evidence-based guidelines, web-based registration of clinical data made by physicians integrated with administrative data and continuous feedback on the enrolment, and risk-adjusted outcomes are the critical elements of the study, which will provide strong and reliable data to measure and improve quality of colorectal cancer surgical care.

Future challenges will be to enhance this project at regional or national level and will use our experience to set regional and national quality standards.

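### Risk adjustment rests in part on ASA and ECOG grades recorded at the benchmarked hospitals; upward grading drift would modestly improve adjusted results and be credited to benchmarking

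*Protocol article*

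**What the plan says.** The article names its adjustment set in Statistical considerations: "Main covariates will include age, gender, ASA score, CCI, surgery setting (urgent vs. elective), and ECOG". On who records the data, Data collection and quality control says: "Case report forms are filled in for each patient by trained healthcare providers (attendings, residents) or properly trained data managers". The Discussion speaks of "web-based registration of clinical data made by physicians integrated with administrative data".

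The section on key performance indicators sets out how the adjusted figures are used. "Each KPI will be estimated both as unadjusted and risk adjusted", and the aim is to "give each center case-mix adjusted outcomes". Hospitals then see the comparison: "Every 12 months, an anonymized report on volume and KPIs will be delivered to each hospital comparing data of all the participating centers".

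For the before/after analysis, the period up to release of the first benchmarking report is the baseline. Statistical considerations concludes: "Any changes on the outcomes will be, therefore, attributed to the benchmarking effect".

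The safeguards described are general: "Quality control and data authenticity will be performed by data managers and clinical research coordinators". Clinical data are also compared with regional administrative records, and deaths are linked to the regional database. The article describes no re-grading of ASA or ECOG, no monitoring of their distribution, and no analysis without them.

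**The concern.** A risk-adjusted result compares observed events with the events expected from recorded case mix. Linkage to the regional database protects the observed deaths. It does not protect the expected deaths, which depend partly on grades assigned at the audited sites. Recording a patient one ASA class higher raises that hospital's expected deaths and complications, so its adjusted result improves although the patient and the care are the same.

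No manipulation is needed. The study expects awareness of monitoring to change behaviour, and more careful or more complete grading after the first report would be one such change. The retro-prospective design could also mean that grades were recorded under different conditions in different periods.

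Two conclusions are exposed: the before/after effect, because the attribution sentence leaves no room for a change in recording, and the comparison between hospitals if their grading habits differ.

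**Working it through.** The article gives no adjusted rate, power or sample size for this analysis, so there is no figure to reproduce. The check holds true risk and deaths fixed, shifts the recorded grades, and sees what adjustment does.

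**Inputs from the article.** About 800 patients per year; a 54-month study period; enrolment dates of 15 April 2019 to 31 December 2023 (56.5 months); a preliminary analysis at 18 months; 7 hospitals.

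**Assumptions not in the article.** ASA 1 to 4 mix of 8/47/40/5%. 30-day mortality by ASA class of 0.4/1.5/6/20% (steep) or 1/2.5/5/12% (shallow). A share of ASA 2 patients recorded as ASA 3: 10%, 20% or 30%. The 18-month mark taken as the end of the baseline period.

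**Step 1: ASA as the only covariate.** Observed mortality O is the sum of share × risk. Recording a fraction s of ASA 2 as ASA 3 gives expected mortality E = O + s × 0.47 × (risk in ASA 3 − risk in ASA 2).

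- Steep, s = 20%: O = 4.14%; E = 4.14% + 0.2 × 0.47 × 4.5% = 4.56%; O/E = 0.91.
- Shallow, s = 20%: O = 3.86%; E = 3.86% + 0.2 × 0.47 × 2.5% = 4.09%; O/E = 0.94.
- For s = 10%, 20%, 30%: O/E = 0.95, 0.91, 0.87 (steep) and 0.97, 0.94, 0.92 (shallow).

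These are upper-end values, because the plan adjusts for more than ASA.

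**Step 2: other covariates in the model.** This is a simulation of 2,000,000 patients with assumed coefficients, crude mortality 6.0%, and age, CCI, urgency, ASA and ECOG in a logistic model with a period term. There is no true change.

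| Share regraded | ASA 2 recorded as 3 | Also ECOG 0 recorded as 1 |
|---|---|---|
| 10% | OR 0.98 | OR 0.97 |
| 20% | OR 0.97 | OR 0.94 |
| 30% | OR 0.95 | OR 0.92 |

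With no regrading the odds ratio is 1.00. Crude mortality is 6.04% in both periods.

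**Step 3: effect on the before/after test.** Baseline: 800 × 18/12 = 1200. Total: 800 × 56.5/12 = 3767, leaving 2567 afterwards. At an assumed 3% mortality, about 36 and 77 deaths, SE(log OR) ≈ √(1/36 + 1/1164 + 1/77 + 1/2490) ≈ 0.205.

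- OR 0.97: |ln OR|/SE = 0.030/0.205 = 0.15; two-sided rejection about 5.3%.
- OR 0.94: 0.062/0.205 = 0.30; about 6.0%.

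At 6% mortality, as simulated, the SE is about 0.147 and the rates are about 5.5% and 7.0%. With a total of 800 × 54/12 = 3600, and so 2400 afterwards, they barely change. The nominal rate is 5%. The corresponding figure for severe complications was not worked out with the other covariates included.

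**Step 4: hospital comparison (ASA-only model).** If one of 7 equal hospitals regrades 20% and the model is refitted, its O/E is 0.92 (steep) or 0.95 (shallow), and the others rise to about 1.01. If all hospitals shift alike and the model is refitted within that period, every O/E stays at 1.00. For scale, 3600/7 ≈ 514 patients per hospital at 3% gives about 15 deaths and 95% limits of about ±49% on O/E (1.96 × √(0.03 × 0.97/514)/0.03).

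**The case against.** The strongest reply is that the effect is small and partly visible already. ASA and ECOG are two of six named covariates, and the others dilute the bias. Every indicator is also reported unadjusted, so pure grading drift would show as a fall in adjusted mortality with crude mortality flat. A 5 to 8% shift for one hospital lies far inside its funnel limits. Drift is assumed; nothing in the article shows that it has occurred. The article does not state that the before/after analysis is adjusted; that is inferred from the modelling paragraph. It says who completes the form, not who assigns the grade. The covariate list is open, and sensitivity models may sit in a full protocol or analysis plan that is not shown.

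Most of this stands, and it limits the size of the point. It does not remove it. The article itself fixes both the two grades as main covariates and the rule crediting any change to benchmarking. Showing crude results helps only if something says how to read a disagreement, and nothing does.

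A reader might infer more: a spurious fall of 14% and a false-positive rate of 11 to 12%. Those figures arise if ASA, split at class 3, is the only covariate and the share at or above it rises from 40% to 50%; the planned adjustment set is wider. A reader might also infer that hospitals with strict grading are ranked worse, or that sites are manipulating grades. The article describes anonymized reports and funnel plots, not rankings, and gives no evidence of manipulation.

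**Conclusion.** The point holds as a modest weakness. Upward drift in ASA or ECOG grading that differs by period or hospital biases adjusted results toward apparent improvement even when deaths are fully verified; downward drift does the reverse. With about 20% of ASA 2 patients regraded, the spurious before/after odds ratio for mortality is about 0.97, or 0.94 if ECOG drifts too, and the test's error rate rises only slightly. A shift common to all hospitals leaves within-period comparisons unaffected but still biases the before/after contrast.

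This rests on the assumed ASA mix, risks, coefficients and amount of drift, and on the before/after model being adjusted. The bias does not shrink with more patients. What makes it worth correcting is the attribution sentence, which would read a recording change as an effect of the audit.

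**What to change.** 1. In each report, print the share of patients with ASA ≥3 and with ECOG ≥2, by hospital and period.
2. Repeat each adjusted before/after and hospital comparison as a sensitivity analysis without ASA and ECOG, using age, sex and surgery setting, which are already collected. Add comorbidity from administrative records only if the linkage supplies it; the article does not say that it does.
3. Amend the attribution sentence in Statistical considerations so that an improvement seen only in the ASA/ECOG-adjusted model, alongside a shift in grade mix, is not credited to benchmarking. Do not require crude and adjusted results to agree in size, since they should differ when case mix truly changes.

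The cost is one table per report, one extra model per outcome and one amended sentence, with no new data collection. The downside is that the reduced set adjusts less well for true severity, so it belongs beside the main model and should not replace it.

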**Methods:**

The Emilia-Romagna Surgical Colorectal Audit (ESCA) is an observational, multicentric, retro-prospective study, carried out by 7 hospitals located in the Emilia-Romagna region. All consecutive patients undergoing surgery for colorectal cancer during a 54-month study period will be enrolled. Data regarding baseline conditions, preoperative diagnostic work-up, surgery and postoperative course will be collected in a dedicated case report form. Primary outcomes regard postoperative complications and mortality. Secondary outcomes include each center’s adherence to the auditing (enrolment rate) and evaluation of the systematic feedback activity on key performance indicators for the entire perioperative process.

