### Study outcomes

The primary objective of this analysis is to assess the frequency of post-operative complications, unplanned re-interventions, re-admissions, and mortality rates (at 30, 90, and 180 days after surgery).

Secondary outcomes include adherence to the clinical audit by each center (intended as the percentage of enrolled eligible patients) along with the study timeframe and possible positive effects on outcomes, both clinical and economic, of systematic measurement and monitoring.

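### The before/after rule credits benchmarking with any change in any outcome; under no effect, chance alone gives at least one such change in about 21-26% of studies on the narrowest reading, and more on wider ones

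*Protocol article*

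**What the plan says.** The rule is in the last part of the protocol article's Statistical considerations. The period up to the release of the first benchmarking report is the baseline, and "the analysis will evaluate any significant changes occurred afterwards". The next sentence gives the interpretation: "Any changes on the outcomes will be, therefore, attributed to the benchmarking effect".

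Four other statements determine how many comparisons the rule can cover:

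- Study outcomes lists the primary measures as "post-operative complications, unplanned re-interventions, re-admissions, and mortality rates (at 30, 90, and 180 days after surgery", which is six measures.
- Statistical considerations adds "All the analyses will be performed considering tumor location (colon or rectum) as a stratification factor".
- The abstract's Methods paragraph names as a secondary outcome the "evaluation of the systematic feedback activity on key performance indicators for the entire perioperative process". Table 2 lists 15 such indicators.
- The only indication of an error level is "A two-sided 95% confidence interval (95% CI) will be reported as appropriate".

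**The concern.** Taken together, the two sentences look for significant changes across a set of outcomes and credit whatever is found to the audit. Nothing in them ties the conclusion to a chosen outcome, and the interpretive sentence does not distinguish improvement from deterioration. With several outcomes, some nominally significant changes are expected by chance even if feedback does nothing, and the text as written would label them a benchmarking effect.

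This matters because the Discussion presents the impact of auditing and feedback as what ESCA sets out to investigate, and looks ahead to using the experience for regional and national standards. The problem is chance error. It would remain with no time trend, stable enrolment and correct standard errors.

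**Working it through.** The article gives no significance level, power or overall error rate, so there is no stated figure to reproduce.

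**Inputs**

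- Level per test: two-sided 5%. This is an assumption, inferred from the 95% CI sentence.
- Primary outcomes: complications, re-intervention, re-admission, and mortality at three times, so 6. Tested separately in colon and rectum: 6 × 2 = 12.
- Table 2: ten indicators apply to colon and rectum, five to rectum only. By stratum: 10 + 15 = 25. Splitting mortality into three times adds 2 per stratum, and splitting length of stay into two cut-offs adds 1 per stratum: 25 + 2 × 3 = 31. One pooled test per indicator: 15.
- Correlation between tests: not given, so a range is shown.

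**Formula.** For m independent tests with no true effect, P(at least one significant) = 1 − 0.95^m. For favourable changes only, it is 1 − 0.975^m. Correlated cases were simulated with normal test statistics; colon and rectum were treated as independent where tested separately.

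| Family | m | Independent | With correlation |
|---|---|---|---|
| Primary outcomes, one test each | 6 | 1 − 0.95^6 = 26% | 21-23% |
| Primary outcomes by stratum | 12 | 1 − 0.95^12 = 46% | 37-41% |
| Table 2, one test each | 15 | 1 − 0.95^15 = 54% | 46% at 0.3; 36% at 0.5 |
| Table 2 by stratum | 25 | 1 − 0.95^25 = 72% | 65% at 0.3; 55% at 0.5 |
| Table 2 by stratum, cut-offs split | 31 | 1 − 0.95^31 = 80% | 72% at 0.3; 60% at 0.5 |

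The 21-23% takes correlations of 0.2 to 0.4 between outcomes and 0.7 between the mortality times. The same structure in two strata gives 38-41%. A patient-level simulation with nested mortality and illustrative event rates gave 37-39%. For the Table 2 rows, a single common correlation within stratum was used. Correlating only the clinically linked indicators gives 74-78% for 31 tests.

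**Favourable direction only, independent tests**

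- 6 tests: 1 − 0.975^6 = 14%.
- 12 tests: 1 − 0.975^12 = 26%.

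**Power of a single-outcome comparison.** At 800 patients a year, 54 months gives 3,600 patients. If the first report comes at 18 months, the split is 1,200 before and 2,400 after. Assume rates of 10% and 7%, which are not in the article. The pooled rate is (120 + 168)/3,600 = 8%.

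- SE under no change: √[0.08 × 0.92 × (1/1,200 + 1/2,400)] = 0.00959.
- SE under the assumed change: √(0.09/1,200 + 0.0651/2,400) = 0.01011.
- At 5%: Φ[(0.03 − 1.960 × 0.00959)/0.01011] = 0.87.
- At 0.05/12: Φ[(0.03 − 2.865 × 0.00959)/0.01011] = 0.60.

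These power figures ignore the planned hospital random effects and case-mix adjustment, so they only compare the two error levels.

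**The case against.** The strongest reply is that this is a condensed article: error levels and the handling of multiple outcomes usually sit in a full protocol or SAP, which is not shown. That stands for any complaint that a multiplicity method is missing, and no such complaint is made here. The attribution sentence, however, is stated in the article and is wrong as it reads, whatever else exists.

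A second reply is that the text can be read outcome by outcome, with a nominal 5% error for each. Nowhere does it say that one significant indicator proves the audit works, and results shown side by side would let a reader tell one or two chance changes from a broad shift. This is fair, and a reader should not infer that the rule cannot separate an effective audit from an ineffective one. But under the outcome-by-outcome reading each chance change is still credited to benchmarking, so the percentages above remain the chance that the report contains at least one false credit.

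Third, a reader might infer that the rule misfires about three times in four. The documents do not support that as the headline. It needs the widest family, separate colon and rectum tests, and weak to moderate correlation. The before/after paragraph speaks of clinical outcomes, whereas several Table 2 items are process or treatment choices. Using location as a stratification factor also fits one stratified test per outcome.

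Fourth, a reader might infer that the authors mean to credit worsening. The study objectives and the secondary outcomes both speak of possible positive effects, which softens this. The attribution sentence still sets no direction, and restricting it to improvement leaves 14-26% for the primary outcomes if the tests are independent.

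Finally, the effect of the audit is a secondary outcome of an observational pilot whose primary objective is descriptive. That limits the consequence to the attribution claim; the descriptive audit is unaffected.

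**Conclusion.** The concern holds in a limited form. The article fixes a rule that credits any change to benchmarking without a named outcome or a direction. Under no effect, the chance of at least one change to credit is about 21-26% on the narrowest reading (six primary outcomes, one stratified test each), about 37-46% for twelve tests by stratum, and about 36-80% over Table 2, depending on pooling, counting of cut-offs and correlation. All of these rest on an assumed two-sided 5% per test. Every reading is well above 5%, but the documents do not settle which one applies, so no single figure should be quoted. The sentence should be changed before the before/after results are interpreted.

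**What to change.** Replace the attribution sentence with wording to this effect:

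- Name one already collected primary outcome in advance for the before/after comparison, for example severe complications as defined in KPI 9.
- Analyse it once across colon and rectum, with tumor location as a covariate, in the planned case-mix-adjusted model with hospital random effects.
- State that only a reduction whose two-sided 95% CI excludes no change will be described as consistent with, or associated with, benchmarking. It is not attributed to it, because the comparison has no control.
- Report the other outcomes and KPIs with CIs as descriptive, or Holm-adjusted within the primary outcomes. State that an isolated nominal p<0.05 among them is not credited to benchmarking.

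The cost is wording only, with no new data. The downside is that the other outcomes can no longer carry the claim on a nominal p-value. In return, the named comparison keeps its full 5% level (power about 87% rather than about 60% at a twelve-test Bonferroni level, under the assumed rates above). The change addresses chance error only. Confounding by time in an uncontrolled before/after design is a separate issue that it does not cure.
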